**Figure 2 F2:**
[figure not shown]
**Flow diagram of the study protocol.** A flow diagram developed according to CONSORT guidelines
[37], describing the enrolment, randomisation, follow-up and analysis of the study.

Women who meet the inclusion criteria and who provide consent will be randomised into either home-based assessment (intervention) group or clinic follow-up (control) group. The RA at each clinic will carry out the randomization through picking the envelope with the lowest serial number available in the clinic. Each woman will be assigned a personal identification number once they consent to participate in the study. This number will then be used for the randomisation process as well as on every form of the questionnaire instead of the recording of names.

### Study protocol

#### All women - recruitment of women on day 1

After the doctor assesses the woman for eligibility of early medical abortion, the clinical eligibility of the woman to participate in the study will be assessed. Once this is established, the RA will assess the non-clinical eligibility of the woman including criteria such as age, area of residence or ownership of a phone, and whether the woman agrees to follow-up at home or in the clinic.

When a woman fulfils eligibility criteria, she will be provided with participant information, written or RA administered, and asked to give consent to participate in writing. Once the woman has agreed and signed the consent form, she will be randomised to home-based assessment group or clinic follow-up group. All women enrolled in the study will be registered in the trial registry, where personal information and means, location and date of follow-up will be recorded. In case a woman fails to be successfully contacted at the time of follow-up, the reason thereof will be noted in brief in the trial registry as well as further attempts to contact the woman. Women will receive instructions of the follow-up procedure, according to group allocation, on day one.

#### Misoprostol provision on day 3

A nurse or a doctor will supervise the administration of misoprostol to the women returning to the clinic on day three. Misoprostol will be provided and the woman is retained in the clinic for observation during one to five hours, depending on clinic, practitioner and woman’s availability. A clinical provider, commonly a nurse, will record any side effects and the abortion outcome upon discharge. Pelvic examination for confirmation of POC expulsion is not considered standard procedure.

##### Home-based assessment group

The intervention in this study consists of a home-based assessment carried out by the woman herself 10–14 days after an early medical abortion using an LSUP-test. The 10–14 day time frame is influenced by the sensitivity of the LSUP-test (1000 units/litre)
[35]. It has been established that the human chorionic gonadotropin (hCG) levels of women with a gestational age no more than nine weeks drops substantially at 10–12 days after a medical abortion. However using a high-sensitivity pregnancy test or conducting the follow-up too early would result in increased numbers of false positives
[36]. Waiting for four weeks to evaluate the abortion outcome may result in on-going pregnancies with gestation above 12 weeks. In this study setting, abortions are not as readily available after 12 weeks of gestation making an early detection of on-going pregnancy crucial. Women allocated to this group will receive an LSUP-test along with a pictorial instruction sheet (Figure 
1). The women will be followed-up by an RA contacting the women over phone or through a home-visit, 12–15 days after initiation of the medical abortion. This is to ensure that the woman had enough time to carry out the LSUP-test by herself on day 10–14 before the contact with the RA. If the woman is not found at home or cannot be reached over phone, two additional attempts will be made to contact the woman.

#### Instructions for home-based assessment group

RAs will use a prototype of the LSUP-test to demonstrate how to use it along with the pictorial instruction sheet. Means of follow-up and date and time will be decided upon according to the woman’s preference. If the woman has a phone and is willing to receive a phone call, this will be the primary choice of follow-up. When women do not have access to a confidential phone, a home-visit will be suggested as an alternative. If the woman prefers neither they are advised to come back to the clinic for follow-up after having conducted the LSUP-test at home. These women will only meet with an RA at the time of follow-up – no clinical care will be offered unless the woman presents with complications or a positive LSUP-test, this will be recorded accordingly.

#### Follow up of home-based assessment group on day 12–15

At the time of follow-up, the RA will record the outcome of the LSUP-test along with side effects and other complications as reported by the woman. The women have been informed to return to the clinic in case of a positive LSUP test. However, the RA will refer the women that have not yet returned by the time of the follow-up visit to the clinic. To understand whether women are capable of assessing their abortion outcome using and interpreting the LSUP-test by themselves, different questions in the research questionnaire have been included. This is to distinguish whether the RA assisted the woman to conduct the LSUP-test at the time of follow-up or whether the woman had done it and interpreted it herself in advance of the RA consultation. In addition to the LSUP-test result the following set of questions will be asked by the RA to screen for other complications as well as the woman’s capacity to assess any side-effects: Do you think your abortion is complete? Did you see expulsion of products? If you had any pregnancy symptoms before are they gone now? Did you bleed more than twice as much as a normal period after taking the pill? Do you still have heavy bleeding? Do you still have severe abdominal pain? Do you feel sick? Have you had fever? Do you feel weaker than usual or like your whole body are aching? If the answer is yes to any of these questions, the RA may choose to refer the woman to the clinic regardless of the result of the LSUP-test. Important to notice is that the pictorial instruction sheet as well as the instructions given in the clinic emphasize the side effects or danger signs requiring a clinical visit. Hence the role of the RA is not to assess the abortion outcome of the woman during the follow-up visit. Moreover, women are not obliged to follow the advise of the RA to return to the clinic. Women with a negative LSUP-test, assessed as complete abortion at the time of follow-up, will be censored out of the study. Women that present with a positive LSUP test but do not return to the clinic will be approached through phone calls or home visits to confirm their abortion outcome in retrospect. Clinical records will be monitored in case of any adverse events or additional procedures in relation to the abortion for up to one-month post abortion.

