### Definitions

In this study, we define complete abortion as when no signs of pregnancy or retention of product of conception (POC) is present, or upon a negative LSUP test, and no further treatment is needed for termination of the pregnancy. We define incomplete abortion as partially retained POC, sometimes with an enlarged size of the uterus or a positive LSUP test. Incomplete abortion requires further treatment, preferably with additional misoprostol or manual vacuum aspiration (MVA). We define on-going pregnancy as persistent pregnancy symptoms, no POC expulsion and enlargement of the uterus
[19]. Moreover, with the LSUP-test we are referring to the combined low- and high- sensitivity pregnancy test purchased from VEDA.LAB (http://www.vedalab.com). The high-sensitivity component is equal to a standard pregnancy test and has a sensitivity of 5 units/litre. The low-sensitivity component has a sensitivity of 1000 units/litre, and is suitable for the use to assess abortion outcome at 10–14 days post abortion. In this study, the low-sensitivity component is of interest, however since there are no separate LSUP tests available on the market we used the combined test. Moreover, the test used in this study is not available in India, however several international pregnancy test manufacturers are currently working to develop LSUP-tests, and its availability on the market is likely to increase in the near future.

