Research assistants cannot be blinded at the time of randomisation, since different instructions are to be given to the women according to their group allocation. The lack of blinding is regarded a limitation in the study design. Important to notice is that the health care providers remain blinded at the initial encounter when the woman is assessed for eligibility of medical abortion as well as when location of misoprostol administration is decided. However, RAs are not blinded when administering the follow-up acceptability interview. Due to poor literacy among the majority of women in the study the acceptability questions cannot be self-administered. However, the follow-up acceptability interviews will be conducted in a confidential setting where no service providers are present. This is to avoid potential bias in the women’s responses regarding acceptability.

It is important to consider that the women in the home-based assessment group are aware that they will be followed-up at 12–15 days after their medical abortion. This may influence their care-seeking behaviour in response to the LSUP-test result as well as their acceptability of the intervention. The study essentially aims to evaluate a self-assessment regime, however due to the need of follow-up, whether home visit or phone call, in the study design the intervention is not a complete self-assessment, rather a home-based assessment followed up by a non-clinical provider. Although the role of the RA is not to assess the abortion outcome of the woman, she will refer the woman to the clinic if she feels any reason to do so. To further evaluate the feasibility of self-assessment, operational research is needed.

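### The home-arm referral sentence turns on a yes to any of nine questions, but for three of them yes is the favourable answer, which conflicts with the protocol's own signs of on-going pregnancy

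*Protocol article*

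**What the plan says.** The section on follow-up of the home-based group on day 12–15 introduces the questions this way: "In addition to the LSUP-test result the following set of questions will be asked by the RA to screen for other complications". The list opens with "Do you think your abortion is complete? Did you see expulsion of products? If you had any pregnancy symptoms before are they gone now". It goes on to past bleeding, then "Do you still have heavy bleeding? Do you still have severe abdominal pain? Do you feel sick? Have you had fever", and ends with weakness or aching. One sentence covers all nine: "If the answer is yes to any of these questions, the RA may choose to refer the woman to the clinic". It applies whichever way the LSUP test came out.

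The Definitions section states: "We define on-going pregnancy as persistent pregnancy symptoms, no POC expulsion and enlargement of the uterus".

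Three other provisions bear on the point:

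- A positive test is handled separately: "The women have been informed to return to the clinic in case of a positive LSUP test". The RA refers those who have not yet returned by the time of her contact.
- The Discussion says of the RA that "she will refer the woman to the clinic if she feels any reason to do so".
- Women with a negative test who are assessed as complete are censored at that contact. Clinical records are then monitored for up to one month.

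**The concern.** The list mixes two kinds of question. For most of the later ones, *yes* reports a problem. For the first three, *yes* reports that things went well. A single trigger of *yes* to any question cannot serve both kinds. For the two questions that match the protocol's own signs of on-going pregnancy, the answer that would raise suspicion is *no*, and a *no* never satisfies the sentence.

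The criterion applies whatever the test showed, so it is the only written, question-based route to the clinic for a woman whose test is negative. The home-based group section calls early detection of on-going pregnancy crucial in this setting, because abortion is less readily available after 12 weeks. The people applying the sentence are non-clinical RAs, who are told that it is not their role to assess the abortion outcome. They therefore depend on the text to say which answers count.

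**Working it through.** The document gives no figure to reproduce here. The check is logical: apply the sentence as written to the possible answers.

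**Inputs.** There are nine yes/no questions (day 12–15 section). The criterion is met if at least one answer is *yes*. The Definitions section supplies two signs that the questions cover: no expulsion is *no* to question 2, and persistent symptoms is *no* to question 3. Its third sign, an enlarged uterus, is not asked about.

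**Direction of each question.** In questions 1–3 *yes* is favourable. In questions 5–9 (continuing heavy bleeding, severe pain, feeling sick, fever, weakness or aching) *yes* is unfavourable. Question 4, on past bleeding, is less clear-cut but leans the same way as 5–9.

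**Applying the sentence.**

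| Woman's report | Q1 | Q2 | Q3 | Q4–9 | Criterion met? |
|---|---|---|---|---|---|
| Complete, no complaint | yes | yes | yes | all no | Yes |
| Thinks not complete, no expulsion, symptoms persist, no other complaint | no | no | no | all no | No |
| As the row above, but feels sick | no | no | no | one yes | Yes, through Q7 only |
| No expulsion, symptoms persist, but believes it complete | yes | no | no | all no | Yes, through Q1 only |

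**Counting patterns.** There are 2^9 = 512 possible answer patterns. An any-*yes* criterion fails only when all nine answers are *no*, so 1 pattern fails and 511 meet it. With questions 2 and 3 both *no*, 2^7 = 128 patterns remain. Of these, 127 meet the criterion, each because of some other question. These are counts of patterns, not of women, and the patterns are not equally likely. They show two things: the answers to questions 2 and 3 that match Definitions never trigger the sentence by themselves, and the one pattern left out includes both of them.

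**Can the frequency of the gap be computed?** It would be the product of four terms:

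1. P(on-going pregnancy)
2. P(false-negative or misread test, given 1)
3. P(*no* to all nine questions, given 1 and 2)
4. P(RA does not refer on her own judgement, given 1 to 3)

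The Discussion gives 1–2% for the first term, and the document gives nothing for the other three. Letting each of those run from 0 to 1 yields anything from nil to the full 1–2%, which is not an informative range.

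**The case against.** The strongest reply is that this sentence is not a binding gate. It says the RA may choose to refer, and the Discussion lets her refer for any reason. A woman who says she saw no expulsion and still feels pregnant can be sent to the clinic anyway, and a woman who says all is well need not be. The main detector of failed abortion is the LSUP test, and a positive result has its own route. The instruction sheet lists danger signs, and records are monitored for a month. Definitions classifies outcomes and does not set referral criteria. Finally, the article condenses a questionnaire and manual that are not shown, and the home-arm procedures were field-tested in 33 women, so a slip in turning a form into prose is quite plausible.

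Most of this stands, and it limits the consequence. It does not remove the error. No sentence in the article reverses the direction for questions 1–3, and this is a rule stated wrongly, not a detail left to another document.

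A reader might infer three stronger things that the document does not support:

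- *That the size of the harm can be read from the protocol's rates.* With 716 / 2 = 358 women per arm, 0.95 × 358 = 340 might say *yes* to a reassuring question, and 0.01 to 0.02 × 358 = 3.6 to 7.2 might have an on-going pregnancy. These count women to whom the wording would apply, not wrong or missed referrals. Meeting the criterion only opens an option, and most of the conditions for a missed case are unquantified.
- *That the clinic arm has the same faulty trigger.* It does not. There the questions serve to record side-effects, a doctor assesses the outcome, and no referral rule is attached.
- *That the primary comparison is biased.* This is possible but not shown. An unexamined home-arm failure counted as complete would favour non-inferiority. Needless referrals could add treatment and work the other way. The document fixes neither the size nor the net direction.

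**Conclusion.** The referral sentence is wrong as written: its single *yes* trigger runs against the meaning of the first three questions and against the signs of on-going pregnancy in Definitions. That conclusion rests on the text alone, and on reading the sentence as covering all nine questions, which is what it says.

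The practical reach is limited. It is confined mainly to a woman in the home-based group with a false-negative or misread LSUP test, *no* to every question, and an RA who does not use her wider discretion. Such a woman may be recorded as complete and censored. The frequency cannot be derived from the document. Whether RAs in the field would follow the literal wording depends on a questionnaire and manual that are not shown.

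**What to change.** Reconcile the referral sentence in the day 12–15 section with the Definitions section. For each of the nine questions, state which answer opens the RA's option to refer. Then check that the home-arm questionnaire and the RA manual code the answers in the same direction. The clinical content of the criterion is for the investigators to decide, and none is proposed here. The cost is one revised sentence and one check of two existing documents. Sample size and analysis are unaffected.

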##### Clinic follow-up group

Women in the clinic follow-up group will be encouraged to return to the clinic for a routine clinical examination by a doctor, 10–14 days after initiation of the medical abortion. In this study, women returning to the clinic will also be assessed with an LSUP-test carried out by clinical staff, and the same set of screening questions as stated above are asked to record any side-effects.

#### Follow-up of clinic follow-up group on day 10–14

Women allocated to the clinic follow-up group will be treated according to the routine practice of each clinic. For the cause of the study the time of the follow-up visit has been standardized to 14 days after initiation of medical abortion, or within the range of 10–14 days. At the follow-up visit, a doctor will assess the outcome of the abortion including a pelvic examination if regarded as necessary. Subsequently, an RA will carry out the final interview in the clinic before the woman will be censored out of the study. Women returning to the clinic will be reimbursed for their travel expenses (INR 200), while women that do not return for clinical follow-up will be reminded to return to the clinic over phone, where possible.

All women

#### Additional procedures, extra visits or lost to follow-up

Clinical staff will record any additional procedures (MVA, repeat misoprostol etc.) provided during the follow-up visit or at the time of misoprostol administration in the clinic, in the research questionnaire. For women returning before their scheduled follow-up with complications or adverse events, a doctor or a nurse will provide appropriate services. This will be recorded in an interim visit form as well as the clinical records of each study site. In addition, women will be asked at the time of follow-up, whether she had any interim visits or additional contacts with any clinic in relation to her abortion. Hence additional treatment or procedures will be recorded in the follow-up questionnaire as per the woman’s report. This is to register all additional procedures or visits of the women, since not all women may return to one of the study sites for interim visits. However, where possible and in the cases of surgical intervention the clinical reports kept by the women will be reviewed to distinguish the abortion outcome of the woman as well as confirm the procedure reported by the woman. Women where no clinical records are available and that are lost to follow-up will be approached through phone-calls, where applicable, or home visits during outreach activities in the villages within three months of their abortion, to confirm the abortion outcome.

### Ethical considerations

This study addresses abortion, commonly considered a sensitive topic due to the context and the social stigma. Therefore, extra measures to maintain the safety and confidentiality of the study participants are necessary. To address this we have developed a confidentiality protocol for each encounter with the women. At the time of enrolment, the women will be explained the study thoroughly and an informed consent will be taken from each woman, administered by the RA. The procedure of consent taking is carried out in a private setting, where none other than the woman and the RA are present, unless the woman is illiterate and a witness is required where this will be solved according to the woman’s preference of witness. Women, allocated to the home-based assessment group, will be able to choose means of follow-up appropriate to their personal situation: phone, home or clinic. At the time of follow-up of the home-based assessment group, two additional households will be visited and camouflage-interviews with young women will be conducted. This is to maintain confidentiality of the women and reduce suspicion from their neighbours. If, at any time during follow-up or interview with the study participants, another person interrupts the interview, the topic will be changed immediately to not reveal the purpose of the visit. If complete privacy cannot be maintained at the time of follow-up, the RA will come back at another time or meet the woman elsewhere at her convenience. If the woman prefers to discontinue the study due to privacy issues, the RA will not try to conduct the follow-up interview. The woman is allowed to exit the study at any time without giving a reason for doing so. These efforts are explained to the woman at the time of enrolment to avoid confusion at the event of topic change or camouflage interviewing.

### Measures

#### Socio-demographic and reproductive background data

Measures such as age, marital status, education level, caste and residential area will compile the socio-demographic information about the study participants. Moreover, the personal reproductive history will be recorded as number of births, number of living children, previous abortions, caesarean section and contraceptive use. Haemoglobin and the gestation will also be measured and recorded.

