### Sample size

The success rate of medical abortion is 95%
[31,32] resulting in a complication rate estimation of 5% in both groups. The primary outcome define the sample size estimation where the 5% non-inferiority margin (delta) establishes the non-inferiority of the home-based self-assessment following medical abortion as compared to the routine clinic follow-up. The delta margin is defined by the clinical assessment standpoint where a 5% difference does not have clinical importance. To proof the non-inferiority of the intervention at a significance level of α = 0,05 and a power of 80%, 596 women are needed. The lost to follow-up estimation of 20%, based on field-testing in the study area, resulted in a final sample size of 716 women. A two-sided 95% confidence interval (CI) (or a one-sided 97,5% CI) will determine the difference in percentage of women requiring surgical intervention from the two groups.

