### Randomisation procedure

The randomisation list will be generated using a computerized random number generator (random allocation software 2.0
[34]). The staff generating the list and preparing the opaque sealed envelopes are not to be involved in any data collection. The randomisation procedure is visualised in the flowchart (Figure 
2). Randomization of the study participants will occur after the first clinical encounter with the doctor. Subsequently, the service provision will occur in a uniform and standard manner regardless of group allocation or study participation. Further blinding is not possible since the means of follow-up are depending on the group allocation. The clinical procedure on day one and three will remain the same regardless of group allocation of the woman. However, the location of misoprostol administration on day three, at home or in the clinic, is agreed upon based on the providers’ assessment together with the woman’s preference. Thus, this decision is made before the enrolment in the study. Block randomisation will be applied to ensure equal distribution of the two study groups in each clinic. Each clinic will be provided with envelopes according to their caseload. Consequently, the number of study participants will vary in each clinic.

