### Secondary study outcome

*The secondary outcomes* include acceptability of the home-based assessment and the home use of misoprostol, when applicable, measured at the time of follow-up. To evaluate acceptability, we will ask women of their choice of method and means of follow-up in the event of a future abortion. Additional acceptability questions will regard women’s advice to a sister or a friend in need of an abortion. Finally, we will ask women with previous abortion experience to compare their previous experience with their current experience. For the purpose of efficacy of the intervention, we will evaluate recordings of the number of, and reasons for interim visits related to the medical abortion as well as side effects including infections, bleeding and pain. In addition, we aim to evaluate contraceptive uptake at 10–15 days after medical abortion along with previous use of contraception. Finally, the time consumed while travelling to and waiting in the clinic will be assessed as reported by the woman at the time of follow-up.

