### Data analysis

SPSS 20.0 will be used for statistical analysis. All analyses will be by intention to treat (ITT) and some will be analysed using per protocol analysis in addition to ITT. The non-inferiority hypothesis will be tested at a significance level of 5% (α = 0,05). Categorical outcomes will be presented using descriptive statistics and compared using χ^2^-test. Numerical variables will be assessed for significance using the student’s t-test. Intergroup comparison will be made between the clinic follow-up group and the home-based assessment group. Differences between groups will be analysed using relative risks (95% CI) and logistic regression for the relative differences. P-values equal to or lower than 0.05 will be considered statistically significant. Acceptability measures will be analysed descriptively, using numbers and percentages of women in the different categories.

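### The named group comparisons carry no baseline covariate; adjusting contraceptive uptake for previous use could gain some precision, while the gain for the primary outcome is very small.

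*Protocol article*

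**What the plan says.** - **Background data** (Socio-demographic and reproductive background data): contraceptive use is listed as part of the reproductive history, and "Haemoglobin and the gestation will also be measured and recorded". Gestation of up to nine weeks is also an inclusion criterion, so it is known before allocation.
- **Place of misoprostol use** (Randomisation procedure): home or clinic is agreed between provider and woman, and "this decision is made before the enrolment in the study". The Discussion adds that providers are blind to allocation when it is decided.
- **Non-inferiority assessment** (Sample size): "A two-sided 95% confidence interval (CI) (or a one-sided 97,5% CI) will determine the difference" in percentages between the groups. The section words this in terms of surgical intervention; I take it as the interval meant for the 5-point margin.
- **Other comparisons** (Data analysis): "Categorical outcomes will be presented using descriptive statistics and compared using" a chi-square test. Numerical variables get Student's t-test, and group differences get relative risks with 95% intervals. Logistic regression is added for relative effects. No covariate is named for any of these.
- **Contraceptive uptake** (Secondary study outcome): the plan is to evaluate "contraceptive uptake at 10–15 days after medical abortion along with previous use of contraception". The Data analysis section does not say how the two are combined.

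**The concern.** A chi-square test and a t-test cannot use a covariate, and none is attached to the interval for the difference or to the relative risks. Randomisation is blocked within clinic only, so the design does not balance gestation, place of misoprostol use or contraceptive history.

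The document gives reasons to think that some of these matter. Women who take misoprostol in the clinic are observed for one to five hours. Extra procedures, including repeat misoprostol, can be given then, and clinically administered additional misoprostol counts towards the failed-abortion rate. Previous contraceptive use is the natural baseline value for contraceptive uptake.

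At stake are some precision and protection against chance imbalance. The validity of the trial is not in question.

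**Working it through.** **Inputs from the protocol**
- Failure 5% in each arm (Sample size): "resulting in a complication rate estimation of 5% in both groups".
- Margin 5 points (Sample size): "5% non-inferiority margin (delta) establishes the non-inferiority of the home-based self-assessment".
- Size and power (Sample size): "at a significance level of α = 0,05 and a power of 80%, 596 women are needed". The Discussion gives 298 evaluable per arm.
- Home use of misoprostol about 40% (Study setting).

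**Inputs that are assumed:** every association between a covariate and an outcome, because the protocol gives none.

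**Step 1: reproduce the plan's figure.** With one-sided 0.025, matching the two-sided 95% interval, n per arm = (1.96 + 0.8416)² × 2 × 0.95 × 0.05 / 0.05² = 7.849 × 38 = 298.3. That is 298 or 299 per arm depending on rounding (596 or 598 in total), so the stated 596 reproduces. One-sided 0.05 gives 470 and does not.

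**Step 2: unadjusted reference.** SE = √(2 × 0.95 × 0.05 / 298) = 0.01785. The 95% half-width is 1.96 × 0.01785 = 3.50 points. Power = Φ(0.05/0.01785 − 1.96) = Φ(0.84) = 80.0%.

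**Step 3: primary outcome, adjusted.** For a binary covariate with prevalence q and failure rates f₀ and f₁ averaging p = 5%, R² = q(1 − q)(f₁ − f₀)² / [p(1 − p)]. Adjustment multiplies the variance of the risk difference by 1 − R².

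| Assumed covariate | Failure rates | R² | Equivalent N (596 × (1 − R²)) | Power at 298 per arm |
|---|---|---|---|---|
| Gestation, two halves | 4% v 6% | 0.0001/0.0475 = 0.2% | 595 | 80.1% |
| Gestation, two halves | 3% v 7% | 0.0004/0.0475 = 0.8% | 591 | 80.3% |
| Gestation, two halves | 2% v 8% | 0.0009/0.0475 = 1.9% | 585 | 80.7% |
| Place, 60/40 | 4% v 6.5% | 0.00015/0.0475 = 0.3% | 594 | 80.1% |
| Place, 60/40 | 3% v 8% | 0.0006/0.0475 = 1.3% | 589 | 80.5% |

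The gain is therefore 0.1 to 0.7 points of power, or about 1 to 11 women. If 20% of the planned 716 are lost, 716 × 0.8 ≈ 573 remain (286 per arm). Power is then 78.4%, and R² = 2% raises it to 79.2%. An optimistic joint R² of 5% at 298 per arm would give 81.9% and a half-width of 3.41 points.

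**Step 4: contraceptive uptake, adjusted for previous use.** The formula is the same, with assumed uptake rates.

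| Share with previous use | Uptake with v without | Overall uptake | R² |
|---|---|---|---|
| 30% | 70% v 55% | 59.5% | 2.0% |
| 30% | 64% v 44% | 50% | 3.4% |
| 30% | 80% v 50% | 59% | 7.8% |
| 40% | 80% v 40% | 56% | 15.6% |
| 50% | 70% v 30% | 50% | 16.0% |

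Interval width scales with √(1 − R²). R² = 2% narrows it by about 1%, and R² = 16% by about 8% (√0.84 = 0.917).

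**Step 5: room for covariates.** Expected failures are 596 × 0.05 ≈ 30 in total.

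**The case against.** The strongest objection is that a reader might infer that every planned comparison is unadjusted, and the text does not say so. Logistic regression is planned, it is the usual route to adjustment, and a journal article may leave its covariate list to an analysis plan that is not shown. That stands: the absence of a list is not in itself a fault. What remains is narrower. The regression is directed at relative effects, and adjusting a logistic model does not narrow the interval for the odds ratio. Unless its predictions are standardised to a risk difference, it adds nothing to a comparison with an absolute margin. The methods that are fixed for the difference and for categorical outcomes carry no covariate.

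Further objections, and what stands of each:
- **Nothing is invalid.** Correct. An unadjusted randomised comparison is unbiased; this is an improvement, not the repair of an error.
- **A larger primary gain needs implausible inputs.** Also correct. Reaching about 3% of variance (17 women) takes failure of 8% v 0.5% by place of use, a sixteen-fold contrast with no support in the document.
- **Not all covariates are clearly available.** Partly right. No section says that the agreed place of misoprostol use is recorded. The actual place on day 3 arises after randomisation and is not a safe substitute. The time at which contraceptive history is recorded is not stated either, although history should refer to the period before allocation.
- **Place of use is only loosely tied to uptake.** Right. The Adaptation phase section allows contraception at the first encounter as well as at clinic misoprostol, so home users are not excluded. Uptake therefore needs only previous use as covariate.
- **Clinic, as the blocking factor, should take priority as a covariate.** Fair, but adjustment for clinic is a separate question. It draws on the same 30 or so events, which is one more reason to keep the list short.

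**Conclusion.** The point holds as a minor, optional improvement. A material gain is plausible only for contraceptive uptake, at about 2–16% of variance. For the primary risk difference the gain is about 0.2–2% of variance and under 1 point of power, so the reason to adjust there is protection against chance imbalance. All these ranges rest on assumed associations.

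A reader might go further and infer that the trial gives up meaningful power on its primary comparison. With a 5% failure rate, the calculation does not support that. Nor does the document support treating all three covariates as ready to use, since the record of the agreed place of misoprostol use is unconfirmed.

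**What to change.** - **Contraceptive uptake:** replace the chi-square comparison with a standardised risk difference, or a linear model with robust standard errors, adjusted for previous contraceptive use. Confirm that previous use is recorded at enrolment or refers only to the time before it.
- **Primary risk difference:** in the same way, adjust for gestation and, if it is recorded, the place of misoprostol use agreed before enrolment. Do not use the actual place on day 3. Judge the 5-point margin on the risk-difference scale and show the unadjusted result beside the adjusted one.
- **Timing:** fix the covariates and the method before outcome data are seen by arm.

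The cost is analysis wording and slightly more analysis work. Gestation and contraceptive history need no new data; the agreed place of misoprostol use needs a check that it is on a form. The primary model should hold no more than these two covariates.
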